### Sample Size

The composite remission rate in Chinese adults with IMN under treatment of immunosuppressive agents in clinical practice in a single center in China was 73.7% (Jiang et al., 2021). An analysis of our retrospective unpublished data from three hospitals in China showed that composite remission rate of IMN patients received CHM alone or combination therapies in clinical practice was 67.0% (75/112). Under the assumption of 10% of loss to follow-up and two-sided alpha level of 0.05, enrolment of 2000 patients would provide 80% power to detect the 2-year composite remission rate.

### Statistical Plan

Attempting to ensure equivalence in baseline characteristics of participants between the CHM group and the conventional therapy group, a propensity score method will be performed. Variables involving age, sex, proteinuria, eGFR, serum albumin, uric acid, PLA2R antibody level, and pathological type will be included into the logistic regression model to calculate a propensity score for each participant. Participants who are exposed to CHM will be matched to those who receive conventional drugs alone based on the propensity score, using the greedy matching with a standard calliper width of 0.2 and without case replacement. Covariate balance of the matched cohort will be assessed using the mean standardized differences. When a |d| > 0.10, it is considered as an imbalance. Inverse probability of treatment weighting based on the propensity score will also be performed to evaluate the robustness of the matching results.

Baseline demographic variables will be presented as means, medians, or percentages, and using Chi-square test, independent t test, or Mann-Whitney *U* test, as appropriate. Outcomes of composite remission, CR, PR, no response, death, relapse, and composite endpoint will be analysed by using Chi-square test and logistic regression. Odd ratios and 95% confidence intervals will be estimated. Time to remission will be analysed by using Cox regression model, adjusting for gender, age, baseline proteinuria, GFR, PLA2R antibody level, uric acid, Chinese medicine syndrome, and propensity score.

Subgroup analysis will be performed on age, gender, diagnosis criteria (i.e., biopsy proven or anti-PLA2R positive), PLA2R positive or negative, blood lipid levels, different risk levels of progressive loss of kidney function, “incident patient” and “prevalent patient”, Chinese medicine syndromes, different assay methods for serum creatinine and proteinuria, different levels of CHM exposure, treatment regimens (CHM alone, conventional medication alone and the combination), conventional medications, and CHM with and without immunosuppressive effect. For the analyses of Chinese medicine syndromes, besides Chi-square test between groups of patients with and without dampness syndrome, a trend test will be performed to assess the dose-response relationship between dampness syndrome and clinical outcomes. CHM with immunosuppressive effect will be defined as either herbal formulas or proprietary CHM products which contain either *Tripterygium wilfordii* Hook. f, *Tripterygium hypoglaucum* (Levl.) Hutch and *Sinomenium acutum* (Thumb.) Rehd. et Wils (Menispermaceae, SA) or their compounds (Zhao et al., 2012; Chen et al., 2014; Pei et al., 2016; Lv et al., 2019; Zheng et al., 2019).

GFR will be estimated by 2009 CKD-EPI creatinine equation and 2021 CKD-EPI creatinine-cystatin C equation. As the 2021 equation has not yet been validated in the Chinese population, analyses involved eGFR will use the estimates calculated by the 2009 equation, and sensitivity analyses based on the 2021 equation will be performed. To eliminate the acute effect, incident patients who experience a serum creatinine increase of more than 30% within 12 weeks after initiated treatments will be excluded in analyses on endpoints in terms of ESRD, 40% eGFR reduction, and eGFR slope.

Additionally, in order to assess the risk of performance bias, the change of prescription pattern before and after the commencement of the study will be analyzed.

All analysis will be tested with a two-sided alpha level of 0.05. For the missing data, the reasons why the data is missing will be analyzed, and multiple imputation will be used.

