Studies showed that CHM could be an alternative monotherapy or adjunctive therapy for adults with IMN. Two case reports suggested that 1 year treatment of the herb *Astragalus membranaceus* Fisch. ex Bunge alone was associated with complete remission in patients who were presenting with nephrotic syndrome and resistant to cyclosporine and mycophenolate (Ahmed et al., 2007; Leehey et al., 2010). A retrospective case series comprised of 15 IMN cases who did not respond to immunosuppressive therapies received 6 months treatment of Jian Pi Qu Shi formula, and 80% of them reached complete or partial remission on the 12th month after treatment (Shi et al., 2018). Chen et al. reported a randomized controlled trial that compared multi-ingredient CHM to conventional immunosuppression with prednisone and cyclophosphamide for IMN patients with nephrotic proteinuria (urinary protein excretion ≥3.5g/24h) (Chen et al., 2013). Composite remission (either complete or partial remission) showed a similar rate in the two arms at 48 weeks (73% vs. 78%) (Chen et al., 2013). Liu et al. compared the remission between IMN patients who received tripterygium glycosides tablets (compound of the herb *Tripterygium wilfordii* Hook.f.) plus prednisone and who received tacrolimus plus prednisone (Liu et al., 2015). Both composite remission (86.9% vs. 90.0%) and complete remission (52.2% vs. 46.7%) were similar between the two groups at 36 weeks (Liu et al., 2015).

These findings were obtained in the setting of clinical trials and need validation in daily clinical practice, as the treatment scenario of CHM is more complicated in practice than that in trials. Instead of a fixed formula or proprietary CHM used through the whole research period in clinical trials, prescriptions of CHM are individualized and changed flexibly based on syndrome differentiation or state of the illness in clinical practice. Therefore, we proposed the first registry-based cohort study of INM in China.

The aims of this registry-based cohort include (but are not limited to):

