### Study Setting

In order to collect a representative sample, the nephrology departments in 11 tertiary-care hospitals across multiple regions in China will recruit and enroll patients continuously. The 11 study sites include Guangdong Provincial Hospital of Chinese Medicine, Guangdong Provincial Hospital of Integrative Medicine, The First People’s Hospital of Zhaoqing, Liuzhou Hospital of Chinese Medicine, and Yue Bei People’s Hospital in south China; Hubei Provincial Hospital of Traditional Chinese Medicine in southwest China; Jiangsu Provincial Hospital of Chinese Medicine and the First Affiliated Hospital of Anhui University of Chinese Medicine in east China; Heilongjiang Institute of Traditional Chinese Medicine and First Affiliated Hospital of Heilongjiang University of Chinese Medicine in northeast China; Shanxi Traditional Chinese Medicine Hospital in northwest China.

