### Eligibility Criteria

Eligible candidates for the study are IMN patients of any risk levels to capture a broad spectrum of clinical presentations. Inclusion criteria include Chinese adults aged from 18 to 85 years old; diagnosis of biopsy-proven IMN or antibodies against phospholipase A2 receptor (PLA2R)-positive patients who are not associated with other diseases which cause secondary MN, such as systemic lupus erythematous, infections with hepatitis B virus, hepatitis C virus, or syphilis, sarcoidosis, and cancer. Patients with the following criteria will be excluded: patients with a GFR less than 15 ml/min/1.73 m^2^; patients with comorbidities including malignant cancers, decompensated cirrhosis, hematologic diseases, and mental diseases.

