### Enrollment and Follow-Up

This study is designed to be a long-term longitudinally extensible cohort. The study aims to include 2000 Chinese IMN adults. The recruitment is estimated to take 42 months, from July 2020 until December 2023. The patients who meet the inclusion criteria will be enrolled continuously. Both incident patients and prevalent patients will be recruited by physicians in nephrology clinics and inpatient departments in 11 participating sites. Incident patients are individuals who are newly diagnosed and first initiated on treatments. Prevalent patients are individuals who have already been diagnosed as IMN and have been receiving treatments before the study. Meanwhile, the electronic medical record in 11 participating sites will be retrospectively screened to recruit the confirmed cases.

Individuals who are eligible and consent to participate will be invited to attend a baseline visit. Participants will be followed for up to at least 2 years. Participants who experience the primary endpoint (remission) will be continued to be followed up until the end of the study or death. The schedule of follow-up visits is presented in Figure 1. Follow-up visits will occur quarterly in the first year after enrollment and then semi-annually from the second year. The baseline, semi-annual, and annual follow-up visits in the first year and annual visits from the second year are required in-person visits. All other visits can be in-person or remote via telephone call or smartphone applications. In order to retain participants and minimize the number of dropouts and withdraws as well as the missing data, a reasonably flexible visit time window within a range of 4 weeks forward or backward from the scheduled visit day will be acceptable.

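### The fixed propensity score omits hospital type, incident/prevalent status, time since diagnosis, prior treatment and syndrome, and includes a biopsy variable some patients lack, so the main CHM comparison may stay confounded

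*Protocol article*

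**What the plan says.** **Score.** Protocol article, Statistical Plan: "Variables involving age, sex, proteinuria, eGFR, serum albumin, uric acid, PLA2R antibody level, and pathological type will be included into the logistic regression model". CHM-exposed patients are matched on this score to patients on conventional drugs alone (greedy, calliper 0.2, no replacement). An absolute standardised difference above 0.10 counts as imbalance. Inverse probability of treatment weighting (IPTW) with the same score is the robustness check. The Discussion relies on the score to limit selection bias.

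**Outcome models.** Composite remission and the other binary outcomes "will be analysed by using Chi-square test and logistic regression". No covariates are named for that regression. The Cox model for time to remission has a named list, which includes Chinese medicine syndrome but not centre, incident/prevalent status or prior treatment.

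**Who enters.**
- Study Setting: recruitment is in "the nephrology departments in 11 tertiary-care hospitals across multiple regions in China". By name, 8 are Chinese medicine institutions, 1 is an integrative medicine hospital and 2 are People's Hospitals.
- Enrollment and Follow-Up: "Both incident patients and prevalent patients will be recruited by physicians in nephrology clinics and inpatient departments in 11 participating sites". Prevalent patients "have been receiving treatments before the study".
- Eligibility Criteria: entry requires "diagnosis of biopsy-proven IMN or antibodies against phospholipase A2 receptor (PLA2R)-positive patients", so a biopsy is not a condition of entry.
- Introduction: "prescriptions of CHM are individualized and changed flexibly based on syndrome differentiation or state of the illness in clinical practice".

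**The concern.** A propensity score balances what is put into it and whatever correlates with that. Three groups of factors that the protocol itself makes prominent are left out.

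- **Hospital type.** With 9 of 11 sites being Chinese or integrative medicine hospitals by name, where a patient is treated plausibly governs whether CHM is given. If remission also differs by hospital type for reasons other than treatment, the CHM contrast becomes partly a contrast between hospitals.
- **Treatment history.** A prevalent patient's enrolment proteinuria and albumin are post-treatment values, and partial remission is judged against peak proteinuria, which may predate enrolment. Equal proteinuria at enrolment does not make a part-treated and an untreated patient comparable.
- **Syndrome.** This is a prescribing driver that the protocol names. It is adjusted for in the Cox model and absent from the score.

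Pathological type raises the opposite problem. It is in the score but unavailable for patients without a biopsy. A complete-case logistic model would drop them. The general statement that multiple imputation will be used would mean supplying a histology that was not observed.

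At stake is the primary comparison. Every listed covariate could meet the 0.10 limit while an unlisted one does not, and the planned check would not show it.

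**Working it through.** **1. Is there a plan figure to reproduce?** None bears on this point. The sample size of 2000 does not enter the argument except as a total to divide among sites.

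**2. Where each omitted factor appears.**

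| Factor | In the score | In the Cox list | Elsewhere in the analysis |
|---|---|---|---|
| Centre / hospital type | no | no | not used in matching |
| Incident/prevalent status | no | no | subgroup |
| Prior treatment, time since diagnosis | no | no | indirectly, via the incident/prevalent subgroup |
| Chinese medicine syndrome | no | yes | subgroup |
| Pathological type | yes | no | diagnosis criteria are a subgroup |

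**3. Illustration for hospital type.**

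Assumptions not given in the documents: equal site sizes, the CHM-use rates, and a 10-point remission difference by hospital type unrelated to treatment.

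Patients at general sites: 2 × 2000/11 = 364. Patients at other sites: 9 × 2000/11 = 1636.

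Spurious risk difference = (general-site share in the conventional group − general-site share in the CHM group) × remission difference by hospital type.

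Standardised difference d = (a − b) / √{[a(1−a) + b(1−b)]/2}, where a and b are the two shares.

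| CHM use, general/other | CHM group (general) | Conventional group (general) | Shares a, b | a − b | d | Spurious difference |
|---|---|---|---|---|---|---|
| 40%/70% | 1291 (145) | 709 (218) | 30.8%, 11.3% | 19.5 pts | 0.49 | 2.0 pts |
| 30%/80% | 1418 (109) | 582 (255) | 43.7%, 7.7% | 36.1 pts | 0.91 | 3.6 pts |
| 20%/90% | 1545 (73) | 455 (291) | 64.0%, 4.7% | 59.3 pts | 1.60 | 5.9 pts |

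The result scales directly with the assumed hospital effect. At 5 points the spurious difference is 1.0, 1.8 and 3.0; at zero there is none. For scale, the two remission rates cited under Sample Size differ by 73.7 − 67.0 = 6.7 points.

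**4. Simulation under assumed strengths.** There were 200 replicates with N = 1800, IPTW and a true CHM effect of zero. Incident/prevalent status and hospital type were generated independently of the scored covariates.
- Score without the two factors: standardised differences of 0.19 to 0.44 for prevalent status and 0.36 to 0.77 for hospital type. The spurious effect was −0.7, −3.5 and −6.6 points under weak, moderate and strong assumptions. In the weak case hospital type had no effect on remission.
- Score with both factors: standardised differences about 0 and bias of 0.2 points or less.

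**5. Effect on error rate.** With 900 per group, remission of 70% and no true effect, a 2-point bias raises the two-sided 5% error to about 15%, and a 3-point bias to about 28%. With 500 per group the figures are about 11% and 18%.

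**6. What exact matching on hospital type would cost.** Assuming 1:1 matching, the ceiling on pairs is the sum over hospital types of the smaller group.
- 30%/80%: 109 + 327 = 436, against 582 conventional patients (25% fewer).
- 20%/90%: 73 + 164 = 237, against 455 (48% fewer).

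Matching within single centres cannot do better.

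**The case against.** **The documents do not rank the drivers of CHM use.** A reader might infer that the omitted factors are the strongest determinants and will certainly stay unbalanced. The protocol gives no CHM use by site. The drivers it names are syndrome and state of illness, and the listed laboratory variables cover much of the latter. Covariates correlated with the omitted factors may also remove part of the imbalance. This stands: the supportable words are 'plausible determinants' and 'may remain confounded'.

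**Mitigations are planned.** Incident versus prevalent and diagnosis criteria are both prespecified subgroups. The incident stratum largely removes prior-treatment confounding, and the biopsy-proven stratum should have histology. This softens the problem, but neither subgroup balances the main comparison, and IPTW inherits the same omissions.

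**The outcome analysis is not just a chi-square test.** A reader might infer an unadjusted primary test, or that centre is missing from every outcome model. Logistic regression is also planned, and its covariates may be set in a fuller plan. The absence of centre is shown for the score and the Cox list only. How matched pairs are handled is likewise ordinary detail for a fuller plan.

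**An article condenses.** That would answer a silence. Here the article states the list of score variables, so the choice can be judged as written.

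**A biopsy may exist.** Some PLA2R-positive patients may have had one, so it is wrong to suppose that histology is absent for all of them. It will be absent for those who did not.

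**Cost.** If hospital type is decisive, overlap is poor and matching within it is expensive, as step 6 shows. This stands, and it shapes the remedy.

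**Conclusion.** The point holds in limited form. The score as fixed omits five plausible confounders that the protocol itself brings into view, and it includes one variable that is undefined without biopsy. The safeguards described do not close the gap for the main comparison.

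The omissions are certain; the size of the consequence is not. The range of about 2 to 6 points rests on assumed site sizes, assumed CHM use and an assumed 10-point hospital effect. Weaker assumptions give less, such as 0.7 points in the weakest simulation.

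The 6.7-point gap is only a yardstick. A reader might take it as the planned difference, but the Sample Size section cites two rates and does not say that their difference is the effect to be detected.

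**What to change.** 1. Add to the propensity model, for both matching and IPTW: incident/prevalent status, time since diagnosis, immunosuppression before enrolment, baseline dampness syndrome, and hospital type (centre where both groups are adequately represented).
2. Report the standardised difference for each added factor against the 0.10 limit.
3. Code pathological type with a separate 'not biopsied' level, instead of dropping or imputing these patients.
4. Adjust the logistic regression already planned for the primary outcome for the same factors.
5. Leave current immunosuppression out of the score. The regimens compared are CHM alone, conventional drugs alone and the combination, so it is part of the exposure. Conditioning on it would leave patients on CHM alone with few or no comparators.

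**Cost.** Mainly analysis wording: medical history, prescriptions and the dampness scale are already to be collected, and the recruiting site is known. It should be confirmed that the medical history captures the date of diagnosis and treatment before enrolment. The statistical price is reduced overlap. Restricting matches within hospital type could lose 25% to 48% of the pairs otherwise possible under the two stronger scenarios. Covariate adjustment or IPTW with an explicit overlap check is therefore preferable to exact matching on centre.

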## Introduction

Membranous nephropathy (MN) is an autoimmune disease that affects the kidney glomerulus. It is the leading cause of nephrotic syndrome in nondiabetic adults, counting for 20–37% in most ages and up to 40% in patients over 60 (Ronco and Debiec, 2015; Couser, 2017). The incidence of MN is 10–12 per million persons per year in Europe and the USA, (Maisonneuve et al., 2000), and a rising incidence has been reported in China (Zhang et al., 2017). Approximately 80% of the cases are idiopathic and 20% of them are pathogenically associated with other systematic diseases (i.e., secondary MN). Optimal supportive care and therapy are applied to all patients with idiopathic MN (IMN) (Floege et al., 2019). Immunosuppressive therapy is recommended for IMN patients at risk for progressive kidney injury (e.g. decreasing glomerular filtration rate [GFR]) or with severe life-threatening nephrotic syndrome (Floege et al., 2019). Glucocorticoids combined with cyclophosphamide or calcineurin inhibitors, as well as rituximab, are the major treatment regimens for IMN patients at different risks. They are effective and also accompanied with risks including toxic effects and a high incidence of relapse. For rituximab, the high cost is a large obstacle to acceptability for patients. Other medicines, such as botanicals which include Chinese herbal medicine (CHM), are also widely used in treating IMN in China (Xu et al., 2015).

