### The Primary Aim

• To summarize the treatment patterns in daily practice for IMN patients in China, and to evaluate the effectiveness in terms of clinical remission among IMN patients who receive different treatment regimens, including CHM, conventional drugs, as well as the combination of both therapies.

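### The main matched contrast does not separate immunosuppressive from supportive drugs, so any-CHM versus conventional drugs alone mixes the CHM effect with differences in immunosuppressant use

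*Protocol article*

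**What the plan says.** The protocol article's primary aim is effectiveness across "different treatment regimens, including CHM, conventional drugs, as well as the combination of both therapies". The Statistical Plan turns this into one matched comparison: "Participants who are exposed to CHM will be matched to those who receive conventional drugs alone based on the propensity score". The score is built from "Variables involving age, sex, proteinuria, eGFR, serum albumin, uric acid, PLA2R antibody level, and pathological type". The Cox model for time to remission adjusts for gender, age, baseline proteinuria, GFR, PLA2R antibody, uric acid, Chinese medicine syndrome and the propensity score. Inverse probability weighting with the same score is the robustness check.

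The three regimens appear in the Statistical Plan only as subgroup factors: "treatment regimens (CHM alone, conventional medication alone and the combination), conventional medications".

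Three other sections bear on who falls into these groups:
- The Introduction states "Optimal supportive care and therapy are applied to all patients with idiopathic MN (IMN"), and then "Immunosuppressive therapy is recommended for IMN patients at risk for progressive kidney injury" or with severe nephrotic syndrome.
- Eligibility Criteria states "Eligible candidates for the study are IMN patients of any risk levels to capture a broad spectrum of clinical presentations".
- Sample Size takes its 73.7% remission rate from patients "under treatment of immunosuppressive agents in clinical practice", and its 67.0% (75/112) from patients on CHM alone or in combination.

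**The concern.** By the article's own account, conventional treatment has two layers: a supportive layer given to everyone and an immunosuppressive layer given to some. The groups are formed as if there were only one. The matched contrast can then answer several questions at once: what CHM adds to an immunosuppressant, how CHM compares with an immunosuppressant it replaces, and how CHM compares with supportive care. These effects need not agree in size or direction, and a pooled estimate weights them by whatever mix of co-treatment each arm happens to contain. Since the primary aim is effectiveness by regimen, a pooled answer does not meet it.

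**Working it through.** **The plan's own figure.** Sample Size gives 2000 enrolled for 80% power, two-sided 0.05, 10% loss, without stating the contrast. If it is 73.7% v 67.0% at 1:1 with pooled variance:

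n per group = [1.960·√(2 × 0.7035 × 0.2965) + 0.842·√(0.737 × 0.263 + 0.670 × 0.330)]² / 0.067² ≈ 729.

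That is 1458 evaluable and 1458/0.90 = 1620 enrolled. With 2000 enrolled (900 evaluable per group) the power is 87.6%. The stated pair of 2000 and 80% is not reproduced at 1:1; an unstated allocation near 2.5:1 would come close. This neither supports nor refutes the present point. What matters here is that the only non-CHM rate used for planning comes from immunosuppressive agents.

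**The two readings of conventional drugs.**

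| | Supportive drugs count | Only immunosuppressants count |
|---|---|---|
| Conventional alone | Supportive-only and immunosuppressed patients pooled | Immunosuppressed patients only |
| Supportive care, no CHM, no immunosuppressant | In the comparator | In no regimen |
| CHM + supportive care, no immunosuppressant | Combination | CHM alone |
| CHM + immunosuppressant | Combination | Combination |
| Exposed arm of the matched contrast | With and without immunosuppressant | With and without immunosuppressant |
| Fit with the 73.7% rate | No | Yes |

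The exposed-arm row is the same in both columns, so that part of the problem does not depend on the definition.

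**Covariates.** None of the eight propensity variables and none of the listed Cox covariates is immunosuppressant use. At equal measured severity, the two arms can still differ in co-treatment. Weighting by the same score inherits the gap.

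**Crude illustration, first reading.** Let s be the supportive-only share of the comparator and r their remission rate. The documents give neither, so both are assumptions.

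Comparator rate = 73.7 − s(73.7 − r). Setting this equal to 67.0 gives s = 6.7/(73.7 − r).

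- r = 20%: 6.7/53.7 = 12.5%
- r = 35%: 6.7/38.7 = 17.3%
- r = 50%: 6.7/23.7 = 28.3%

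**The same arithmetic, second reading.** The comparator stays at 73.7%. Suppose CHM has no effect and a share u of the CHM arm takes no immunosuppressant and remits at r. The CHM arm's rate is then 73.7 − u(73.7 − r), which equals 67.0% at the same shares. A gap of the planned size could therefore come from co-treatment alone.

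**The case against.** **A condensed article may leave the drug list elsewhere.** Which drugs count as conventional could be set out in the full protocol or analysis plan, neither of which is shown. That stands for the definition alone. It does not settle the point: the article itself fixes the contrast, the matching and the covariates, and the any-CHM arm can mix immunosuppressed and other patients under either definition.

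**The text leans towards immunosuppressants only.** The Introduction describes prednisone with cyclophosphamide as conventional immunosuppression, and Sample Size already refers to patients on CHM alone. This is fair. A reader might infer that the CHM-alone group is nearly empty, or that the comparator certainly mixes supportive-only and immunosuppressed patients. The documents support neither. No regimen counts are given, the statement about supportive care is general background, and the mixed comparator follows only if supportive drugs count as conventional.

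**Severity is partly controlled.** The score includes proteinuria, eGFR, albumin and PLA2R antibody, which relate to the risk that prompts immunosuppression. Subgroups by risk level, regimen and conventional medication are also planned. Both give some protection. But balancing severity does not balance the treatment chosen at a given severity, and subgroup analyses leave the main comparison as it is.

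**The figures are crude.** A reader might infer that the CHM result will change sign. The calculation cannot show that. It uses unmatched rates from different sources and an assumed r, and it holds CHM at 67.0% while the comparator's case mix moves. Under matching, low-risk supportive-only controls would be paired with similar CHM patients, so both rates would shift.

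**Conclusion.** The concern holds in this form: the main matched contrast pools regimens that differ in immunosuppressant use, and nothing in the listed adjustment captures that difference. It follows from the article's own statements and needs no assumption about which definition of conventional drugs is used. Two further consequences are conditional and mutually exclusive: a mixed comparator that departs from the 73.7% planning rate, or supportive-only patients with no regimen. The size of the resulting bias cannot be derived from the documents. The break-even share of about 12% to 28% shows only that a modest imbalance could matter, on crude rates and with assumed supportive-care remission of 20% to 50%. It predicts neither a reversal nor a particular bias in the matched analysis. The protocol should be changed, and the repair needs no new data.

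**What to change.** Treat supportive drugs as background and classify every patient at the start of follow-up by two factors: CHM yes/no and immunosuppressant yes/no. Each patient then has a cell. Name these as the main propensity-matched contrasts, with the score re-estimated within each:

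1. CHM + immunosuppressant v immunosuppressant.
2. CHM without immunosuppressant v immunosuppressant.
3. CHM without immunosuppressant v supportive care only.

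No separate exact match on immunosuppressant use is needed. It is automatic in the first and third contrasts, where both arms have the same status, and impossible in the second, where they differ by definition. State whether herbal products with immunosuppressive effect count towards the second factor or stay within CHM; the Statistical Plan already defines them for a subgroup. If a pooled any-CHM contrast is kept, report it as secondary.

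The change is one of analysis definition and does not touch care. Data Collection and Management already provides for recording prescriptions of both CHM and conventional drugs. The cost is smaller matched sets, and so less precision, in each contrast.

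### Centre is absent from the propensity score, the matching rule, the Cox list and the chi-square test, so the regimen comparison can be confounded by hospital

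*Protocol article*

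**What the plan says.** - **Sampling.** Under Study Setting, "the nephrology departments in 11 tertiary-care hospitals across multiple regions in China will recruit and enroll patients continuously". By name, eight of the sites are Chinese-medicine institutions, one is integrative and two are general people's hospitals. The Interventions section says there is no treatment protocol and no interference with therapy.
- **Primary comparison.** The Statistical Plan states: "Outcomes of composite remission, CR, PR, no response, death, relapse, and composite endpoint will be analysed by using Chi-square test and logistic regression". No covariates are listed for the logistic model.
- **Propensity score.** Eight variables are named: age, sex, proteinuria, eGFR, serum albumin, uric acid, PLA2R antibody level and pathological type. Matching is greedy, with a calliper of 0.2 and no replacement. It is not restricted to patients of the same hospital. Inverse probability weighting on the same score is the robustness check.
- **Time to remission.** "Time to remission will be analysed by using Cox regression model, adjusting for gender, age, baseline proteinuria, GFR, PLA2R antibody level, uric acid"; the list ends with Chinese medicine syndrome and the propensity score. That makes eight terms, none of them centre.
- **Subgroups.** The long subgroup list has no entry for centre.

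**The concern.** The primary aim includes comparing remission between CHM, conventional drugs and their combination. In a cohort where each hospital follows its own practice, hospital can be a common cause of regimen and of recorded outcome. It can influence who receives CHM, and it carries differences in co-treatment, referral and laboratory measurement that bear on remission. The eight propensity variables are patient-level and balance only what they measure.

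If hospital acts on both sides, a matched pair may consist of a CHM patient from a Chinese-medicine hospital and a conventionally treated patient from a general hospital, with similar proteinuria and eGFR. The contrast is then partly between hospitals. The p-value is nevertheless computed as if the only uncertainty came from about 1800 unrelated patients. Weighting on the same score carries the same gap, so agreement between matching and weighting would not show that the result is free of it.

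The protocol's own planning figures show how regimen and hospital can coincide. The immunosuppressive rate of 73.7% comes from one centre, and the CHM rate ("combination therapies in clinical practice was 67.0% (75/112") from three others' or overlapping hospitals' records. The article does not say how far that gap reflects regimen and how far it reflects hospital.

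**Working it through.** **The plan's own figure.** The Sample Size section says "enrolment of 2000 patients would provide 80% power to detect the 2-year composite remission rate", with 10% loss and two-sided alpha 0.05. Taking 73.7% against 67.0% (75/112 = 66.96%) with equal groups, 80% power needs 729 per group. That is 1458 evaluable, or 1458/0.9 = 1620 enrolled. With 2000 × 0.9 = 1800 evaluable, power is 87.6%. A figure of 80% at 2000 arises only at an unstated split of roughly 2.4–2.6 to 1. This mismatch is a separate matter and is not evidence on centre. For the present point, it matters only that the section mentions no allowance for centre.

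**Inputs.**
- From the document: 11 hospitals; 1800 evaluable; average hospital size m = 1800/11 = 163.6.
- Assumed, because the document gives neither: outcome ICC 0.01 to 0.05; variation in CHM use between hospitals, expressed as an exposure ICC from 0 to 0.25. Also assumed: equal hospital sizes, 70% remission and no true regimen effect.

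**What the exposure ICC means here.** It is the between-hospital variance of CHM share divided by p(1 − p).
- Nine hospitals at 80% and two at 20%: p = (9 × 0.8 + 2 × 0.2)/11 = 0.691. Variance = [9 × (0.109)² + 2 × (0.491)²]/11 = 0.0536. ICC = 0.0536/0.2136 = 0.25.
- Nine at 70% and two at 30%: p = 0.627. Variance = [9 × (0.0727)² + 2 × (0.327)²]/11 = 0.0238. ICC = 0.0238/0.2338 = 0.10.

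**Approximation.** The variance inflation of the unstratified comparison is about 1 + (m − 1) × ICC(outcome) × ICC(exposure). At 0.05 and 0.25 this is 1 + 162.6 × 0.0125 = 3.03. The false-positive rate is then 2 × [1 − Φ(1.96/√3.03)] = 26%.

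**Simulation** (beta-binomial, 11 × 164 patients, 20,000 runs; share of null trials declared significant by the plain chi-square test):

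| Exposure ICC | Outcome ICC 0.01 | 0.02 | 0.05 |
|---|---|---|---|
| 0 (equal CHM use) | 4.8% | 4.9% | 4.3% |
| 0.10 | 6.9% | 8.0% | 13.4% |
| 0.25 | 10.0% | 13.8% | 24.9% |

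A centre-stratified Cochran-Mantel-Haenszel test stays at 4.7% to 5.2% in every cell. A separate simulation with logit-normal centre effects and the 80%/20% shares gives 10% and 26% at outcome ICC 0.01 and 0.05.

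**Where the excess comes from.** In the 80%/20% scenario, at outcome ICC 0.01 and 0.05:
- random 1:1 matching across hospitals, then the plain chi-square: 8% and 21%;
- 1:1 matching within hospital, then the same plain chi-square: 4.5% and 4.9%.

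The same test holds its level once hospitals are balanced. The excess is therefore confounding by centre.

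**The case against.** **The inflation is conditional.** A reader might infer that the error rate is inflated as a matter of fact. The document does not support that. Both CHM share and remission must vary by hospital, and neither is quantified. With equal CHM use the plain test runs at about 5%. This stands, and the size can only be given as a range under assumptions.

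**The chi-square test is not the culprit.** It is tempting to treat this as a fault of the outcome tests alone and leave the propensity list aside. The within-hospital matching result shows otherwise: balancing centre at the design stage removes the excess. A score containing centre would also enter the Cox model, which adjusts for the score. This stands, and the propensity list and matching rule belong at the front of the point.

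**The simulations are not the planned analysis.** They use no patient covariates. Matching on proteinuria, eGFR, albumin and antibody level would remove the part of hospital variation that is case mix. This stands too. The assumed ICC should be read as what remains after those covariates.

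**An unseen analysis plan may add centre.** For the logistic model this is fair: its covariates are not listed, so centre is neither included nor excluded. It is weaker for the propensity and Cox lists, which are written out, and for the named chi-square test.

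**The cohort remission rate.** A reader might also infer that its confidence interval is too narrow. The Statistical Plan gives intervals for odds ratios only and names no method for the cohort rate, so no stated error exists there.

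**Assay methods.** The planned subgroup by laboratory method suggests that measurement may vary, but the text does not tie it to sites. It is weak support only.

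**Conclusion.** The point holds in a conditional form. As written, the plan leaves centre out of the propensity variables, the matching rule, the Cox list and the chi-square test. Patients nevertheless come from hospitals of different types that choose treatment freely. If CHM use and residual remission both differ by hospital, the regimen comparison is confounded by centre, and the planned weighting check would not reveal it.

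Under an assumed outcome ICC of 0.01 to 0.05, the false-positive rate is about 5% with equal CHM use, 7% to 13% at exposure ICC 0.10, and 10% to 25% at exposure ICC 0.25. These figures rest on equal hospital sizes, 70% remission and no covariate adjustment, and they are not estimates for this cohort. No conclusion is drawn about the unlisted logistic covariates or about an interval for the cohort rate.

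**What to change.** In the Statistical Plan:
1. Match within centre, or include centre in the propensity model and show its balance after matching and after weighting.
2. Include centre as a stratum or fixed effect in the outcome logistic model.
3. Stratify the Cox model by centre.
4. For any unmatched comparison, use a centre-stratified (Cochran-Mantel-Haenszel) test in place of the plain chi-square. Do not apply it to pairs matched across hospitals, because it would break the pairs.
5. If a cohort remission rate is reported with an interval, allow for clustering by centre.

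The Sample Size text need not change for this point.

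**Cost.** The change is to analysis wording only and needs no extra patients or visits. Intervals become somewhat wider, and some patients go unmatched. In the 80%/20% scenario with 163 patients per hospital, matching within hospital yields at most 11 × 163 × 0.2 = 359 pairs. Matching across hospitals yields at most 9 × 163 × 0.2 + 2 × 163 × 0.8 = 554. Putting centre in the model avoids the strict within-hospital restriction. Under either approach, hospitals where nearly all patients receive one regimen contribute little, and the report should say so.
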